### 2.2. Study Sample

The study sample for study #1 will be recruited from cancer patients with solid tumors (HR + HER2- breast, or prostate cancer) who have completed cancer therapy (hormone therapy excepted) as this population may benefit the most from increases in NK cell number and activity, perforin, and granulysin to prevent infection as patients become relatively immunocompromised after chemo- or radiation therapy. For study #2, the study sample will be recruited from axial spondyloarthritis patients who have chronic or breakthrough pain, as virtual reality has been shown to reduce pain, and d-limonene administration in animals has shown pain reduction. Since the two studies are set in the future and are pilot studies, we expect for study #1 to recruit and enroll 25 participants and for study #2 to recruit and enroll 25 participants. For study #1, the participant number is limited by budget and the cost of pre-clinical and clinical laboratory tests. For study #2, the participant number is limited by budget and the cost of paper-based tools. Concurrent controls for both studies will be identified by the clinicians in either the cancer clinics or the arthritis clinic. Concurrent controls will meet the same study inclusion and exclusion criteria as those who are enrolled in the study interventions. We expect to have 4 of each of the assigned genders in the control groups. The control groups will be randomized to receive neither SFIT intervention, VR, or atomized phytoncides. They will be exposed to atomized water dispersal for 1 h, the same length of time as the study participants who will receive the SFIT interventions. All the same data will be collected for both study #1 and study #2 on these control participants. At the end of the studies, should an effect of the SFIT intervention be noted, the control participants will have the opportunity to complete the same intervention. Clinicians will lead the recruitment of these patients, followed by a phone screening for inclusion and exclusion conducted by the principal investigator and research associate.

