### 2.4. Intervention—Procedure

Our two studies are novel as no one to date has used simulated forest immersion in patients with acute or chronic morbid conditions. The principal investigator (PI) and research associate (RA) will implement SFIT in a separate room from the room used to cross-check inclusion and exclusion, obtain informed consent, collect baseline measures, and allow the participant to rest. Prior to the arrival of the participant, the SFIT intervention space will be prepared. Preparation of the intervention space includes calibration of the instruments that will measure volatile organic compound particles (phytoncides are volatile organic compounds) and droplets, room temperature and humidity, and room surface temperatures, followed by measurement of the ambient particles and droplets and room temperature and humidity prior to the implementation of the atomized phytoncides [71,81]. Phytoncides α-pinene, β-pinene, and d-limonene (Floraplex Terpenes, Ypsilanti, MI, USA) will be prepared for atomization with a commercially available atomizer (Asakuki 500 mL Premium Atomizer, Tronhon Co., Ltd., Chongqing, China) that can emit phytoncides for up to 3 h. Once the dose expected (0.80 ppm) reaches the dose published by Li [6], the participant will be brought into the intervention room. To date, the Li study, which was conducted with healthy men, has been the only study to record phytoncide dose in a controlled setting. We will use this concentration as the target dose for our humidified phytoncide set up. Both at the beginning and at the end of 1 h of exposure to the simulated forest immersion therapy intervention, ambient phytoncide in the contained space will be measured indirectly by measuring both the increase in ambient air particle mass and number, as well as by measuring the change in total volatile organic compounds (VOCs). Total particle numbers will be measured with a continuous ultrafine particle counter (P-Trak 8525, TSI, Shoreview, MN, USA), and the total VOCs will be measured with the portable handheld monitor (Mini ppbRAE 3000, Honeywell International INC.; San Jose, CA, USA). The P-Trak and Mini ppbRAE 3000 will measure the increase in particle numbers and water droplets (aerosol), respectively, which will serve as a surrogate of relative exposure to phytoncide. Continuous monitoring of room temperature and relative humidity will be measured by the HOBO MX2301 Temperature/RH Data Logger (ONSET, Bourne, MA, USA). Room surface temperature will be measured by ADC Adtemp Mini 432 Non-Contact Infrared Thermometer (American Diagnostic Corporation, Hauppauge, NY, USA). VR will be provided by VIVE Pro Eye, HTC (high-tech computer) Corporation, (New Taipei City, Taiwan) with digital rendering of forested greenspace. Once 1 h of SFIT concludes, the participant will be removed to the preparation area and given instructions related to reporting unanticipated problems, adverse events, and serious adverse events, and an appointment to return for follow up on Day 3. See Figure 1, which illustrates the SFIT process/procedure.

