##### Mini ppbRAE 3000, Honeywell International Inc., San Jose, CA, USA

The ppbRAE 3000 measures volatile organic compounds (VOCs) related to the phytoncides that we are atomizing. The ppbRAE 3000 will be zero-calibrated using a charcoal zero filter and Isobutylene Air Balanced span gas [84]. For two-point calibration, isobutylene at 10 ppm and 100 ppm will be used [85]. During two-point calibration, we will use a set 0.5 LPM regulator. This regulator can handle up to 500 psi, which is the psi of the span gas cylinders and also within the toleration limit of the ppbRAE 3000 regarding pressure and flow. It is important that the gas cylinder connection is CGA 600 and corresponds to the connection on the regulator, meaning that the threading has to be compatible between the cylinder and the regulator. If 500psi is exceeded during calibration or survey mode, the diaphragm within the RAE 3000 may be damaged, leading to inaccurate data collection. In survey mode, data will be updated every 60 s and a data log will be created. The data log will be downloaded using software specific to the ppbRAE 3000 and found online [82].

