##### Asakuki 500 mL Premium Atomizer, Tronhon Co., Ltd., Chongqing, China

The atomizer holds 500 mL of liquid that can be atomized over 3 h. Of that 500 mL, a portion will be reduced that coincides with the amount of phytoncide that will be added. We expect that we will add 30 mL per phytoncide to the atomizer to achieve the detectable published amount [6,21]. Mist will be created by an ultrasonic plate within the atomizer, and the mist will be adjusted for a weak mist or a strong mist. Choice of weak or strong mist will be adjusted to fit the published detectable amount of phytoncide. Mist time can be regulated to maintain 60, 120, and 180 min of operation. We will use a 60 min mist time with the participants of study #1 and study #2. A fan within the atomizer will disperse the mist into the room. Room temperature and humidity will be monitored continuously as low temperature and high humidity may condense the mist into water droplets [87], which is to be avoided to allow for accurate dose calculations.

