##### Phytoncides, Floraplex Terpenes, Ypsilanti, MI, USA

α-pinene, β-pinene, and d-limonene are the phytoncides (forest oils) of interest for SFIT. Interestingly, all three in combination have been tested in normal males in both forest immersion and hotel/sleep contexts and have shown effective elevations in NK cell numbers and activity as well as increased expression of perforin and granulysin [5,6,20,21]. However, these three phytoncides have not been tested in the SFIT context with breast and prostate cancer patients. D-limonene alone has been tested in the context of pain and shown to be effective in an animal model when not paired with VR [88]. All three phytoncides are available as purified isolates in containers of 4, 8, or 32 ounces. The phytoncides will be added to the Asakuki atomizer with an easy calculation of ounces to ml, and that amount will be subtracted from the 500 mL total container in the atomizer so as to maintain a standardized addition of phytoncides:water ratio. Measurement of this mixed mist by ultrafine particulate and VOC survey will be the method of determining the dose of the phytoncide.

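### Phytoncide dose and drop-off rest partly on a total particle count that water mist can move, and the text contradicts itself on what the VOC monitor measures

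*Protocol article*

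**What the plan says.** Section 2.4 (Intervention—Procedure) says that phytoncide in the room is measured indirectly at the start and end of the hour, by "measuring both the increase in ambient air particle mass and number" and by the change in total VOCs. It assigns total particle number to the P-Trak and total VOCs to the ppbRAE 3000. The next sentence says that the two instruments "will measure the increase in particle numbers and water droplets (aerosol), respectively, which will serve as a surrogate of relative exposure to phytoncide". The reference reading described there is of ambient room conditions before atomization starts.

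The phytoncides subsection of 2.4.1 goes further: "Measurement of this mixed mist by ultrafine particulate and VOC survey will be the method of determining the dose of the phytoncide". Under Feasibility and Reliability of Intervention Stability (Section 2.5), readings from both instruments before and after the hour determine dose drop-off, which is tested by t-test at α = 0.05. None of these places ranks one instrument above the other.

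On the liquid, the atomizer subsection says "The atomizer holds 500 mL of liquid that can be atomized over 3 h" and "We expect that we will add 30 mL per phytoncide to the atomizer to achieve the detectable published amount". The phytoncides subsection adds that "that amount will be subtracted from the 500 mL total container in the atomizer", so phytoncide replaces water within a fixed volume. On controls, Section 2.2 says "They will be exposed to atomized water dispersal for 1 h, the same length of time as the study participants" and that the same data are collected on them.

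On the VOC monitor, its own subsection says: "The ppbRAE 3000 measures volatile organic compounds (VOCs) related to the phytoncides that we are atomizing".

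**The concern.** A measure of phytoncide should respond to phytoncide and stay flat when there is none. The P-Trak is described only as counting particles, and nothing says that it separates a phytoncide particle from a water particle. The atomizer emits a mixture that starts as mostly water in the intervention arm and wholly water in the control arm. Against an ambient-air reference, any countable particles from the water mist enter the increase that the protocol calls a surrogate for phytoncide.

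This matters because delivered dose, its consistency and its drop-off over the hour are declared products of these pilots (the feasibility text and Section 3.1). The atomizer subsection also says that the weak or strong mist setting is chosen to match the published amount. If the particle count helps to judge that match, more water mist could pass for more phytoncide. If the two channels disagree on drop-off, the text does not say which one is the dose.

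The description of the VOC monitor compounds the problem. The one channel that could separate phytoncide from water is said, in the key sentence, to measure water droplets.

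**Working it through.** The document states no figure for the water share, so there is nothing to reproduce. The check has two parts.

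**1. Composition of the fill**

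Inputs:
- Reservoir volume: 500 mL (atomizer subsection).
- Expected volume of each phytoncide: 30 mL (atomizer subsection).
- Phytoncide volume is taken out of the 500 mL (phytoncides subsection).
- Number of phytoncides: three in study #1 and d-limonene alone in study #2 (Section 3.1); none in controls (Section 2.2).

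Formula, with k phytoncides: water share = (500 − 30k) / 500.

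| Session | k | Phytoncide (mL) | Water (mL) | Water share |
|---|---|---|---|---|
| Study #1, intervention | 3 | 90 | 410 | 410/500 = 82% |
| Study #2, intervention | 1 | 30 | 470 | 470/500 = 94% |
| Control | 0 | 0 | 500 | 500/500 = 100% |

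If phytoncide were added on top of 500 mL, the shares would be 500/590 = 84.7% and 500/530 = 94.3%. The phytoncides subsection rules that reading out, and it would change little.

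Between the two studies the phytoncide in the fill differs by a factor of 90/30 = 3, while the total volume stays at 500 mL.

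These are shares of the liquid in the reservoir. Turning them into shares of the particle count needs the composition of the mist, droplet sizes, evaporation and particle yield, and the document gives none of these. Two illustrative assumptions show how open the answer is:
- If water droplets leave no countable particle, the water contribution to the count is 0%.
- If the particle rise is proportional to fill volume, the contribution is 82% in study #1 and 94% in study #2, and a control session shows a rise with no phytoncide at all.

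The second case is not a ceiling, and nothing in the document favours either.

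**2. What each instrument is said to measure**

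| Place | P-Trak | ppbRAE 3000 |
|---|---|---|
| Section 2.4, sentence assigning instruments | total particle number | total VOCs |
| Section 2.4, next sentence, read with its word respectively | particle numbers | water droplets (aerosol) |
| Instrument subsections of 2.4.1 | ultrafine particle counter | VOCs related to the phytoncides |

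The middle row conflicts with the other two on the ppbRAE. Particle mass is promised in Section 2.4, but no instrument listed there or in 2.4.1 is described as measuring it.

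**The case against.** The strongest reply is that particle count is never used alone. Every place that names it also names VOCs. By the monitor's own subsection, the VOC reading tracks the compounds being atomized, and a water-only session adds none of them. It is also the only channel calibrated in ppm (span gas at 10 and 100 ppm), so it is the natural reading to set against the 0.80 ppm target. This stands. A reader might infer that the protocol cannot show that one arm was exposed and the other was not, or that it compares particle counts with a ppm target. The document supports neither. The weakness lies in the particle half of the pair and in the absence of any ranking between the halves.

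A second tempting reading is that the mist is 82–94% water, or that this share of the particle signal is false. Those figures describe the expected fill only.

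A third is that controls would be misclassified as exposed. Assignment settles who receives phytoncide, and no participant endpoint is stated to be analysed by particle count.

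The protocol is also alert to moisture. It monitors temperature and humidity, plans cutoff criteria, and wants condensation avoided so that dose calculations are accurate. That limits variation between sessions but does not remove a water-mist contribution from the count.

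It can be argued that a fixed phytoncide-to-water ratio makes particle number a fair relative measure. This fails for controls, where the ratio is zero, and between the studies, where it differs. Within a session it assumes that phytoncide and water decline together, which is not shown.

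Finally, the droplet wording may be shorthand, since the abstract links droplet measurement with VOCs. That may explain the phrase, but it leaves the contradiction in place.

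**Conclusion.** The point holds as a defect in a stated measurement rule. Total particle count has equal standing with total VOCs as surrogate, as determinant of dose and as measure of drop-off. It is not described as specific to phytoncide, and its only stated reference is ambient air. Following the text as written, a change in water mist can be read as a change in phytoncide.

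The planned fill is 82% water in study #1, 94% in study #2 and 100% in controls, assuming the expected 30 mL per phytoncide is used. The size of the resulting error in the particle channel cannot be computed from the document.

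The contradiction over the ppbRAE and the unsupported mention of particle mass need no assumption. The consequence is confined to fidelity and feasibility reporting, where the VOC data remain available as a fallback. It is worth correcting before the pilots report dose and drop-off, but it does not undermine the clinical outcome comparisons.

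**What to change.** - In Section 2.4, the phytoncides subsection of 2.4.1 and the feasibility text of 2.5, base phytoncide dose and the drop-off t-test on the ppbRAE VOC reading. Keep particle number as a check of mist output.
- Where particle counts are reported, show them against the water-only control sessions at the same mist setting and elapsed time. Section 2.2 says the same data are collected on controls. Confirm that this covers the instrument logs.
- Reconcile Section 2.4 with the ppbRAE subsection on what that instrument measures.
- Delete particle mass, or name the instrument that measures it.

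The cost is rewording and a comparison using data the protocol already plans to log, with no added equipment or participants. The downside is that one channel fewer can be quoted as evidence of dose.

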
#### 2.4.1. Intervention—Equipment and Calibration

All instruments will be placed horizontally on a table in the center of the room against one wall with sampling ports directed towards the participant for optimal measurement and dispersal of phytoncides.

##### P-Trak 8525, TSI, Shoreview, MN, USA

The P-Trak is a continuous ultrafine-particle (UFP) counter. The P-Trak has the capability of measuring particles as small as 100 nm. UFPs are currently studied to find associations with specific health effects [82]. The P-Trak will be zero-calibrated for each use using a charcoal filter. Both during the calibration and survey mode, research-grade isopropyl alcohol will be used in a small alcohol cartridge chamber in the instrument. The P-Trak has a data log that updates every minute and has a minimum and maximum range that is noted when the instrument is in survey mode. The data log will be downloaded onto a computer using software specific for the P-Trak [83]. All software will be accessed from the P-Trak website [81].

##### Mini ppbRAE 3000, Honeywell International Inc., San Jose, CA, USA

The ppbRAE 3000 measures volatile organic compounds (VOCs) related to the phytoncides that we are atomizing. The ppbRAE 3000 will be zero-calibrated using a charcoal zero filter and Isobutylene Air Balanced span gas [84]. For two-point calibration, isobutylene at 10 ppm and 100 ppm will be used [85]. During two-point calibration, we will use a set 0.5 LPM regulator. This regulator can handle up to 500 psi, which is the psi of the span gas cylinders and also within the toleration limit of the ppbRAE 3000 regarding pressure and flow. It is important that the gas cylinder connection is CGA 600 and corresponds to the connection on the regulator, meaning that the threading has to be compatible between the cylinder and the regulator. If 500psi is exceeded during calibration or survey mode, the diaphragm within the RAE 3000 may be damaged, leading to inaccurate data collection. In survey mode, data will be updated every 60 s and a data log will be created. The data log will be downloaded using software specific to the ppbRAE 3000 and found online [82].

##### HOBO MX2301 Temperature/RH Data Logger, ONSET, Bourne, MA, USA

The HOBO temperature and relative humidity (HOBO T/RH) data logger, which is suitable for both indoor and outdoor application, is a small portable unit that uses an application (HOBOConnect) loaded onto a mobile device. The app will use a Bluetooth connection to the HOBO T/RH that is easily configurable and logs temperature and relative humidity in real time that you will view on our mobile device, in this case an iPhone. The HOBO T/RH will be placed within a 30 m line of sight towards the participant. Due to the size of the room within which we will set up the intervention, we will use one HOBO T/RH. Data download will be accomplished when the iPhone (mobile device) is within 100 m of the HOBO T/RH unit. Data updates every 2 min with an accuracy of ±0.2 °C and ±3.5% RH [86]. Data software will be downloaded online [84].

##### Measurement of Ambient Room Conditions

Room temperature and humidity may alter the overall measurement of particle number and droplets. Measuring all four of these ambient conditions will allow for consistency in the experimental condition between participants. The room has a set temperature of 70 °F, and since the room is located against a foundation wall, humidity may vary; therefore, it is important to monitor both of these ambient conditions and use cutoff criteria based on average temperature and humidity of the controlled lab setting. We will also use a non-contact infrared surface thermometer to measure radiant heat of room surfaces that may add to the perceived comfort of the SFIT intervention room [81]. The ADC Adtemp Mini 432 Non-Contact Infrared Thermometer (American Diagnostic Corporation, Hauppauge, NY, USA) with a range of 59–77 °F will be used for this purpose. The ambient room air temperature, humidity, and surface temperature date will be collected as a mean prior to, during, and at the end of the intervention.

##### Asakuki 500 mL Premium Atomizer, Tronhon Co., Ltd., Chongqing, China

The atomizer holds 500 mL of liquid that can be atomized over 3 h. Of that 500 mL, a portion will be reduced that coincides with the amount of phytoncide that will be added. We expect that we will add 30 mL per phytoncide to the atomizer to achieve the detectable published amount [6,21]. Mist will be created by an ultrasonic plate within the atomizer, and the mist will be adjusted for a weak mist or a strong mist. Choice of weak or strong mist will be adjusted to fit the published detectable amount of phytoncide. Mist time can be regulated to maintain 60, 120, and 180 min of operation. We will use a 60 min mist time with the participants of study #1 and study #2. A fan within the atomizer will disperse the mist into the room. Room temperature and humidity will be monitored continuously as low temperature and high humidity may condense the mist into water droplets [87], which is to be avoided to allow for accurate dose calculations.

##### Phytoncides, Floraplex Terpenes, Ypsilanti, MI, USA

α-pinene, β-pinene, and d-limonene are the phytoncides (forest oils) of interest for SFIT. Interestingly, all three in combination have been tested in normal males in both forest immersion and hotel/sleep contexts and have shown effective elevations in NK cell numbers and activity as well as increased expression of perforin and granulysin [5,6,20,21]. However, these three phytoncides have not been tested in the SFIT context with breast and prostate cancer patients. D-limonene alone has been tested in the context of pain and shown to be effective in an animal model when not paired with VR [88]. All three phytoncides are available as purified isolates in containers of 4, 8, or 32 ounces. The phytoncides will be added to the Asakuki atomizer with an easy calculation of ounces to ml, and that amount will be subtracted from the 500 mL total container in the atomizer so as to maintain a standardized addition of phytoncides:water ratio. Measurement of this mixed mist by ultrafine particulate and VOC survey will be the method of determining the dose of the phytoncide.

